#### Plans for collection, laboratory evaluation, and storage of biological specimens for genetic or molecular analysis in this trial/future use {33}

Not applicable. No biological specimens will be collected nor stored in this study.

## Statistical methods

### Statistical methods for primary and secondary outcomes {20a}

Descriptive statistics will be used to summarise participants’ baseline demographics and outcome variables throughout the study time points. Attrition analysis and randomisation tests will be carried out to test for differences in demographic and outcome variables between the intervention and comparison groups. Repeated measures ANCOVA will be conducted to examine any significant improvements in the primary and secondary outcomes across baseline and 3-month follow-up assessments whilst controlling for the effects of demographics (i.e. age, sex, education, chronic diseases) and the frequency of intervention sessions. Generalised estimating equation (GEE) analyses will be conducted to compare the primary and secondary outcomes at the 3-month follow-up between the intervention and comparison groups whilst controlling for the effects of demographics and the frequency of intervention sessions. The intention-to-treat principle will be adopted in the analyses for all the primary and secondary outcomes by imputing missing follow-up outcome data with their baseline values (i.e. assuming no change after the intervention for the primary and secondary outcomes) under the assumption of data being missing not at random. This assumption is plausible in the sense that missing data because of dropouts or non-responses are more likely amongst old-old participants with severe health problems. All statistical analyses will be conducted using R software. The treatment effect within and between the two groups will be assessed using Cohen’s *d* statistic [64].

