### Objectives {7}

This study aims to (1) examine the effects of health coaching in community-dwelling older adults with various chronic diseases, and (2) compare the effects of two types of health coaches (i.e. health professionals and lay health workers) on health coaching outcomes. The effectiveness of health coaching is often measured through individual changes in health knowledge and behaviours, psychological status and clinical outcomes [36, 44]. With reference to previous health coaching studies [40, 43, 45, 46], the present study will measure patient activation, physical activity and nutrition behaviours as primary outcomes and depressive symptoms, body mass index (BMI) and systolic and diastolic blood pressure as secondary outcomes. This study hypothesised that the primary and secondary outcomes will be improved after participation in health coaching, and the improvements in health coaching delivered by lay health workers are comparable to those delivered by health professionals.

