### Eligibility criteria {10}

Research assistants will assess the eligibility of interested participants. The inclusion criteria are Chinese adults (1) aged 60 years and above, (2) who live in the community and (3) who are diagnosed with at least one of the following chronic diseases or conditions: hypertension, hyperlipidaemia, diabetes, heart disease, COPD, chronic pain, elevated blood pressure or central obesity. To ensure capabilities in communication and decision-making for daily living, the exclusion criteria are set as follows: (1) have impaired cognitive function (a score ≤ 16th percentile in Montreal Cognitive Assessment 5-min) [48]; (2) have poor functional mobility (Timed Up and Go test ≥ 30 s) [49]; (3) are diagnosed with mental disorders (e.g. schizophrenia or depression) and/or dementia; (4) are not able to communicate in Cantonese, Mandarin, and English; and (5) have severe hearing problem that cannot be corrected by hearing aids.

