#### Intervention description {11a}

The comparison and intervention groups will be assigned to a health coaching intervention. The comparison group will receive a health coaching intervention delivered by health professionals, such as nurses and dieticians, to promote a healthy lifestyle and self-management of chronic diseases. The intervention group will receive the same health intervention, except that it is delivered by lay health workers, including health promotion workers and graduates in health studies. Thus, the procedure and format of health coaching interventions remain the same across comparison and intervention groups whilst the clinical knowledge and experience of health coaches vary between them.

The health coaching intervention implemented in this study is based on effective health coaching components (e.g. motivational interviewing techniques and solution-focused goal setting) identified in systematic reviews and studies of health coaching in chronic disease management [34, 43, 51, 52]. All health coaches must complete over 100 h of training in a health coaching curriculum [53], supplemented with chronic disease-specific content (e.g. symptoms and regimens). The curriculum covers active listening and non-judgmental communication, navigating healthcare systems, setting self-management goals and motivational interviewing techniques. Although older adults may have different chronic diseases, they face similar challenges in managing their health conditions [54]. The chronic disease-specific content thus covers guidance for medication adherence, physical activity, dietary modifications and health monitoring. Due to the pragmatic nature of the study, further supervision processes will not be possible. Similar to previous studies, the health coaching intervention proceeds for 3 months [55, 56], and health coaches provide one-on-one support to older adults with chronic diseases, with a maximum caseload of 20 older adults at any given time. There will be a minimum frequency defined as one in-person or telephone contact every 6 weeks.

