The health coaching intervention in this study takes into account the individual courses of chronic diseases and the emergence and severity of comorbidities and provides a tailored approach to support lifestyle changes. By demonstrating the effectiveness of lay health coaching, this study can empower older adults to take an active role in managing their chronic conditions, fostering their self-efficacy and resilience in the face of age-related deterioration [39]. Furthermore, echoing the recommendations of embracing a diverse set of healthcare providers to improve access to healthcare services [65], this study is dedicated to examining whether lay health workers from diverse backgrounds can provide self-management support as effectively as health professionals. The positive findings of this study will provide evidence for integrating lay health workers into the healthcare system to improve the inclusivity and accessibility of healthcare services, especially for marginalised populations [30]. It will also encourage a collaborative model of chronic disease management where health professionals focus on more complex medical issues of the patients whilst lay health workers address their lifestyle and behavioural changes, thus reducing the power imbalances in favour of health professionals [65] and alleviating the pressure of professional personal shortage in chronic disease management. Furthermore, the potential to standardise health coaching interventions can lead to more uniform practices across different healthcare settings, improving consistency and quality of care.

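### Objective 1 and the within-group treatment effect cannot be answered by this design: both arms are coached, so before-after change does not isolate the effect of coaching

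*Protocol article*

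**What the plan says.** All references are to the protocol article.

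- **Objectives {7}** lists two aims. The first is to "examine the effects of health coaching in community-dwelling older adults with various chronic diseases"; the second is the comparison of coach types. The first half of the hypothesis is that "the primary and secondary outcomes will be improved after participation in health coaching".
- **Intervention description {11a}**: "The comparison and intervention groups will be assigned to a health coaching intervention". The content, procedure and format are shared, and only the coach's background differs.
- **Trial design {8}** gives two measurement occasions, one before the intervention and one directly after it at 3 months.
- **Statistical methods {20a}** assigns a separate analysis to each aim. For change over time: "Repeated measures ANCOVA will be conducted to examine any significant improvements in the primary and secondary outcomes across baseline and 3-month follow-up assessments", adjusted for demographics and session frequency. For the comparison of arms at 3 months it plans GEE. It then says that "The treatment effect within and between the two groups" will be expressed as Cohen's *d*.
- **Discussion** names, as one focus of the study, whether the benefits of coaching extend to this population, and looks ahead to its use with the words "By demonstrating the effectiveness of lay health coaching".

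**The concern.** Randomisation in this trial answers one question: does it matter who delivers the coaching? What coaching itself does is a different question, and it needs an estimate of what would have happened without coaching. No usual-care, waiting-list or other uncoached group supplies that estimate.

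Change from baseline to 3 months therefore combines any effect of coaching with everything else that moves scores over the period:

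- time trend;
- completing the same instruments a second time;
- self-report effects, since the primary outcomes are self-rated scales;
- concomitant treatment, including drug treatment, which section {11d} allows.

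Adjusting for demographics and session frequency does not remove these. If the time effect is significant, the plan's wording licenses reading it as an effect of coaching, although the trial has not isolated one. The same gap limits a finding that the arms are similar, because two equally ineffective arms would also look alike.

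**Working it through.** **Step 1: the plan's own figure.** Sample size {14} uses f = 0.2, power 90%, alpha 0.05 and two equal groups. As a two-group F test with one numerator degree of freedom, the noncentrality is N × f² = 266 × 0.04 = 10.64 and the power is 0.9015 (N = 264 gives 0.8993). Allowing for 30% dropout, 266 / 0.70 = 380. Both figures reproduce, but they size the comparison between coach types and say nothing about objective 1.

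**Step 2: how often a before-after test shows improvement when coaching does nothing.** The documents give neither the drift nor the baseline-to-follow-up correlation r, so both are assumed and varied. A paired t test stands in for the repeated measures analysis, without covariates. With scores in SD units:

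- SD of change = √(2(1 − r))
- noncentrality = drift × √N / SD of change
- probability = chance of a significant result in the direction of improvement (nominal 0.025)

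Example with N = 266 and drift 0.10. At r = 0.5 the SD of change is 1.00 and the noncentrality is 0.10 × 16.31 / 1.00 = 1.63. At r = 0.8 they are 0.632 and 2.58. Exact noncentral-t results for both arms pooled:

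| Drift not due to coaching | r = 0.5 | r = 0.6 | r = 0.7 | r = 0.8 |
|---|---|---|---|---|
| 0.05 SD | 0.126 | 0.147 | 0.181 | 0.250 |
| 0.10 SD | 0.369 | 0.443 | 0.555 | 0.729 |
| 0.20 SD | 0.901 | 0.953 | 0.987 | 0.999 |

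For scale, f = 0.2 in two equal groups is d = 0.4, so these drifts are at most half of the design effect.

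**Step 3: does the planned imputation protect against this?** Section {20a} sets missing follow-up to the baseline value. With 380 randomised and 30% missing, the mean drift shrinks to 0.7 × drift, but the variance of change also shrinks, to 0.7 × 2(1 − r) + 0.21 × drift². For a 0.10 SD drift the probabilities are 0.369 to 0.727, practically unchanged.

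**Step 4: one arm alone, drift 0.20 SD, r = 0.6.** SD of change = √0.8 = 0.894.

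- 133 completers: z = 0.20 / (0.894 / √133) = 2.58, and Φ(2.58 − 1.96) is about 0.73.
- 190 with 30% set to baseline: mean 0.14, SD √(0.56 + 0.0084) = 0.754, z = 0.14 / (0.754 / √190) = 2.56, and the probability is again about 0.73.

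**Step 5: the randomised comparison under the same drift.** In 10,000 simulated trials with 133 per arm, drift 0.20 SD in both arms, r = 0.6 and no coaching effect, the between-arm test of change scores rejected in 0.050 of runs. The pooled before-after test rejected in 0.953 of the same runs. Drift common to both arms cancels in the first test and not in the second.

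**The case against.** The best defence is that the trial is mainly a comparison of coach types. The Abstract says so, the active comparator is justified in {6b} by existing evidence for coaching, and the hypothesis speaks only of improvement after participation. The effectiveness wording in the Discussion is aspirational. This stands as a defence of the randomised comparison. It does not rescue objective 1, which is listed separately and has its own analysis, and {6b} itself says that it is uncertain whether lay coaching works in this population.

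Several stronger readings are tempting, and the documents do not support them.

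- **That regression to the mean drives the results.** Eligibility {10} admits people with "chronic pain, elevated blood pressure or central obesity", so it may affect blood pressure and BMI in those who entered by the last two routes. Both are secondary outcomes, and no one is selected on the primary outcome scores. The section asks for a diagnosed condition, gives no mmHg cut-off and does not make the trial's baseline reading the qualifying one. The size of any regression cannot be derived, and a figure in mmHg would rest on assumptions throughout and apply to a subgroup of unknown share.
- **That the baseline health report distorts follow-up ratings.** It is presented in the first coaching session, so change that it produces belongs to the intervention.
- **That the one-arm false-improvement rate should use all 190.** That gives about 86% at 0.20 SD and r = 0.6, but ignores the planned 30% dropout and baseline imputation.
- **That a time effect will certainly be published as proof of effectiveness.** This is a prediction. What can be shown is that the stated objective and label permit it.

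Dropping within-group Cohen's *d* altogether would also go further than needed. A standardised change is acceptable as a description.

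**Conclusion.** The point holds as one of design and interpretation. Objective 1 and the within-group treatment effect cannot be delivered by two coached arms measured once before and once after. That conclusion follows from the text and needs no numerical assumption.

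Its practical size is only illustrative, because drift and correlation are assumed. With no coaching effect and r of 0.5 to 0.8, a 0.10 SD drift gives a significant pooled improvement with probability about 0.37 to 0.73 at 266 completers, against a nominal 0.025. A 0.20 SD drift within one arm at r = 0.6 does so about 73% of the time after the planned dropout.

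For the primary outcomes the rival explanations are time trend, repeat testing, self-report and concomitant treatment. Regression to the mean is a possible addition for blood pressure and BMI only. A reader might infer that the lay-versus-professional comparison is biased as well. It is not biased by a drift common to both arms, though similarity between them would not by itself establish that either form of coaching works.

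**What to change.** 1. Reword objective 1 and the first half of the hypothesis as describing change from baseline to 3 months in each arm, reported as mean change with a 95% CI.
2. In Statistical methods {20a}, stop calling within-group change a treatment effect. A standardised change may be kept under a descriptive name.
3. Confine causal and confirmatory conclusions to the randomised comparison of lay and professional coaches.
4. State as a limitation, and carry into the Discussion, that without an uncoached arm the trial cannot show that either form of coaching is effective.

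These are changes to wording and to what may be concluded. They need no extra arm, participants or visits. The downside is a narrower claim; keeping objective 1 as a causal question would require an uncoached comparison group.

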### Trial design {8}

This study is a single-blind, multi-centre RCT with a two-group pre-test and post-test between-groups design, in accordance with SPIRIT guidelines [47]. It delivers a 3-month health coaching intervention either by lay health workers (intervention group) or health professionals (comparison group) to community-dwelling older adults with chronic diseases. Survey measurements of primary and secondary outcomes will be taken before and immediately after the intervention. The study will compare the effects of the intervention and control groups at 3 months.

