#### Sample size {14}

The required sample size is estimated for one of the primary outcomes, i.e. patient activation. With reference to previous studies of patient activation interventions on chronic disease self-management [43, 61], the sample size is estimated on the basis of an effect size *f* = 0.2. Using G*Power, power analyses revealed that a total sample size of 266 is required to detect differences amongst the two intervention conditions (i.e. health coaching delivered by lay health workers vs. health professionals), using a multivariate analysis of variance with an effect size of 0.2, a power of 90% and an alpha level of 0.05, with 133 individuals in each condition. Considering the dropout rate of 30% over a period of three months, the target sample size is adjusted to 380 (with 190 individuals in each condition).

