#### Implementation {16c}

After obtaining written informed consent and collecting baseline data, an independent researcher will generate the allocation and inform the study coordinator about the results. To keep the research assistants blind to the allocation, the study coordinator will directly inform the health coaches about the list of assigned participants.

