### Data collection and management

#### Plan for assessment and collection of outcomes {18a}

Baseline and 3-month follow-up assessments will be conducted by trained research assistants to assess the primary and secondary outcomes. A detailed description of the instruments used in the study can be found in the ‘Outcomes {12}’ section. Data will be collected through the online survey platform QuestionPro to minimise data entry errors. All data will be anonymised and saved in a password-protected database on a firewall-protected local network server at City University of Hong Kong. Access to all data will be restricted to authorised study staff. The data will be stored, coded and cleaned in R software before analyses (e.g. checking for duplicates, coding of missing data and date of entry).

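### The 3-month between-arm model does not list the baseline value of the outcome as a covariate, which costs precision (not validity) by an amount that depends on an unstated correlation

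*Protocol article*

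**What the plan says.** Statistical methods {20a} describes two analyses.

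- A repeated measures ANCOVA is used "to examine any significant improvements in the primary and secondary outcomes across baseline and 3-month follow-up assessments", with adjustment for "demographics (i.e. age, sex, education, chronic diseases) and the frequency of intervention sessions". This is where the term demographics is spelled out.
- GEE analyses are used "to compare the primary and secondary outcomes at the 3-month follow-up between the intervention and comparison groups". Their stated adjustment is for the same demographics and for how often sessions took place.

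The second is the arm comparison. Its covariates are named, and the baseline value of the outcome is not one of them. The first uses baseline, but as one of two repeated responses in a test of improvement over time.

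The baseline values will exist. Trial design {8} states: "Survey measurements of primary and secondary outcomes will be taken before and immediately after the intervention". The data collection plan {18a} repeats it: "Baseline and 3-month follow-up assessments will be conducted by trained research assistants to assess the primary and secondary outcomes". Sequence generation {16a} stratifies on age, sex, education and number of chronic diseases, and on no outcome measure.

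**The concern.** For a continuous outcome measured before and after treatment, the baseline value is usually the best single predictor of the follow-up value. If the arm comparison leaves it out, the variation it would explain stays in the residual. Chance differences between arms in baseline activation, behaviour scores, BMI or blood pressure then carry into the estimate, except for the part that the demographics explain. Stratification on demographics does not prevent this.

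Precision matters here because the aim is to show that lay coaching does as well as professional coaching. How firmly that can be said depends on how narrow the interval around the arm difference is.

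**Working it through.** **Inputs.** Sample size {14} plans on f = 0.2 "with an effect size of 0.2, a power of 90% and an alpha level of 0.05, with 133 individuals in each condition", then inflates 266 to 380 for 30% dropout. Allocation is 1:1. The article gives no baseline-to-follow-up correlation r, so r = 0.3 to 0.7 is my assumption. Outcomes are in SD units with equal SDs at both times.

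**1. Reproducing the plan's figure.** For two equal groups d = 2f = 0.4.

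- Normal approximation: n per arm = 2(1.960 + 1.282)²/0.4² = 131.4, so 132 per arm and 264 in total.
- Noncentral F with noncentrality f²N: power is 0.9004 at N = 265 and 0.9015 at N = 266, the first total that gives equal arms.
- Dropout: 266/0.7 = 380.

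Both stated figures reproduce as an unadjusted two-group comparison. No gain from baseline is built in.

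**2. Follow-up-only comparison against ANCOVA.** Adjusting for baseline multiplies the variance of the arm difference by 1 − r². At 133 per arm, power = Φ(0.4/√(2(1 − r²)/133) − 1.96). The difference detectable with 90% power is 3.242 × √(2(1 − r²)/133).

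| r | variance forgone (r²) | reduction in SE | power at d = 0.4 | detectable at 90% |
|---|---|---|---|---|
| none (unadjusted) | – | – | 90.4% | 0.40 SD |
| 0.3 | 9% | 5% | 92.8% | 0.38 SD |
| 0.4 | 16% | 8% | 94.5% | 0.36 SD |
| 0.5 | 25% | 13% | 96.5% | 0.34 SD |
| 0.6 | 36% | 20% | 98.3% | 0.32 SD |
| 0.7 | 49% | 29% | 99.5% | 0.28 SD |

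These are upper figures for the extra gain, because the planned demographic covariates may already explain part of what baseline would.

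**3. If the GEE is an arm-by-time model.** The contrast is then a difference in change scores, with variance proportional to 2(1 − r). ANCOVA has (1 − r)(1 + r). The ratio is (1 + r)/2, so the loss is (1 − r)/2: 35% at r = 0.3, 25% at 0.5 and 15% at 0.7. If the arms are constrained to a common baseline mean, the loss is essentially nil.

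**4. Interaction with the imputation rule.** Section {20a} replaces missing follow-up values with baseline values. With 30% copied, and dropout unrelated to outcome, the analysed correlation becomes about 0.7r + 0.3.

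- r = 0.3 becomes 0.51, and 0.51² = 26%.
- r = 0.5 becomes 0.65, and 0.65² = 42%.

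Part of that apparent gain comes only from the copied values. The same copying shrinks a true difference of 0.4 SD to 0.7 × 0.4 = 0.28 SD, so the interval would be narrower around a diluted estimate.

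**5. Which n applies.** The imputed analysis has 190 per arm, with a nominal unadjusted 95% half-width of 1.96 × √(2/190) = 0.20 SD. The 133 per arm (half-width 1.96 × √(2/133) = 0.24 SD) is the planned evaluable number and matches the complete-case sensitivity analysis.

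**The case against.** The strongest reply is that GEE is a method for correlated responses, and the only correlation the article describes is two assessments per person. The design is called pre-test and post-test, and the hypothesis concerns improvements. Baseline may therefore enter as a response with an arm-by-time term, and an article need not print the model equation. This stands in part: the text does not exclude that reading. However, it names the 3-month outcome as the target and lists the covariates, so omitting baseline is the plain reading. The arm-by-time version still loses 15% to 35% against ANCOVA over the assumed range. Only a constrained-baseline model removes the loss, and none is described.

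It is also fair to say that the planned power is already 90% without baseline adjustment. The sample size is not undermined, and the issue is one of efficiency.

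Three stronger readings are tempting, and the article supports none of them.

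- A reader might infer that the trial certainly discards a quarter or more of its precision. That needs r ≥ 0.5 on the variance scale, or r ≥ 0.66 on the standard-error scale (√(1 − 0.75²) = 0.66). No correlation is given.
- A reader might quote larger power swings for a 0.3 SD difference or a 0.3 SD non-inferiority margin. Neither appears in the article, whose planning difference is 0.4 SD.
- A reader might infer bias. Chance imbalance under randomisation is already reflected in the standard error.

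**Conclusion.** The point holds as a recoverable loss of precision. As written, the between-arm model at 3 months names its covariates and leaves out the baseline outcome, which is collected for every primary and secondary outcome. For r between 0.3 and 0.7, an assumed range, the variance forgone is about 9% to 49%, and somewhat less after demographic adjustment. At d = 0.4 and 133 per arm, power would go from 90% to about 93% to 99.5%. Under an arm-by-time reading the loss is 35% to 15%. The randomised comparison stays valid and the stated sample size stands. The change is worth making because a claim that lay coaching is as effective rests on the width of the interval.

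**What to change.** State the between-arm model for each primary and secondary outcome as the 3-month value on arm, the baseline value of the same outcome and the four stratification factors. Alternatively, specify a longitudinal model with a common baseline mean across arms. Say explicitly whether the baseline record is a covariate or a response. Fix this before any analysis by arm. Whether session frequency, a post-randomisation variable, belongs in the model is a separate question, and the gain above does not depend on it.

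No new data are needed, and 266 and 380 need not change; the gain goes into narrower intervals. There are two small costs.

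- Implementation {16c} puts baseline before allocation ("After obtaining written informed consent and collecting baseline data, an independent researcher will generate the allocation"), while Participant timeline {13} has participants complete the baseline assessment after being randomised. These must be reconciled, so that the covariate is confirmed as a pre-randomisation measurement.
- The change should not be relied on together with baseline-carried-forward imputation, because the copied values make the apparent gain partly artificial. The missing-data method should be reviewed at the same time.

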In health coaching, health coaches take on the role of improving patients’ health literacy and guiding them to set and achieve realistic health goals through educational materials, patient-centred communication and empowerment [24, 25]. On the basis of their clinical experience, health coaches can be broadly categorised into two groups: health professionals and lay health workers [22]. Health professionals encompass various clinical practitioners, such as physicians, nurses, dieticians, pharmacists and students in these fields. By contrast, lay health workers usually do not possess specified credentials or regulated professional status. Examples include certified health coaches, health promotion workers and graduates of health-related fields (e.g. public health, nutrition and physiology). With profound clinical experience in treating chronic diseases and knowledge of medication management, health professionals are primarily considered to fit the role of health coaches [26, 27]. However, lay health workers from various backgrounds account for a growing segment of health coaches over the years [10, 28, 29]. In many low- and middle-income countries, lay health workers are increasingly recognised for their role in improving health equity for marginalised groups [30]. They tend to share similar values, socioeconomic status and/or cultural backgrounds with patients [31], and their interactions with patients are seen as non-hierarchical and less stigmatising than those with health professionals [32, 33]. Thus, patients are more inclined to engage with a health coach who is a lay health worker, particularly when the health coaching intervention is community-based.

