#### Plan for promote participant retention and complete follow-up {18b}

The health coaching sessions will be arranged between health coaches and participants upon mutual agreement. The participants will receive reminders from the health coaches regarding the day and time of the health coaching session. To maximise retention, the health coaching sessions will be conducted in participants’ homes or via telephone. Research assistants will follow-up with and motivate the participants for the 3-month follow-up assessment.

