### Methods in analysis to handle protocol non-adherence and any statistical methods to handle missing data {20c}

Intention-to-treat analysis will be used to minimise the impact of participant dropouts and non-adherence to the protocol by analysing all participants according to their original assignment, regardless of whether they completed the study. Missing data will be imputed using statistical methods to ensure that the analysis is not biased by missing data.

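### The between-arm GEE adjusts for session frequency, a post-randomisation variable, so it estimates coach type at equal contact and not the effect of assignment

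*Protocol article*

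**What the plan says.** Under Statistical methods {20a}, the protocol article gives two models. A GEE is to "compare the primary and secondary outcomes at the 3-month follow-up between the intervention and comparison groups", and it is fitted "whilst controlling for the effects of demographics and the frequency of intervention sessions". A repeated-measures ANCOVA, described as testing improvement from baseline to 3 months, has the same adjustment: "controlling for the effects of demographics (i.e. age, sex, education, chronic diseases) and the frequency of intervention sessions".

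Four other places show what kind of variable session frequency is:

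- Timing. Implementation {16c}: "After obtaining written informed consent and collecting baseline data, an independent researcher will generate the allocation". All coaching follows allocation.
- Number. Intervention description {11a} sets only a floor: "There will be a minimum frequency defined as one in-person or telephone contact every 6 weeks". Section {11b} lets participants stop sessions whenever they ask.
- Arrangement. Section {18b}: "The health coaching sessions will be arranged between health coaches and participants upon mutual agreement".
- Link to coach type. Background and rationale {6a} argues that "patients are more inclined to engage with a health coach who is a lay health worker", particularly in community-based coaching.

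The second objective {7} is to compare the effects of the two types of coach. Sections {20a} and {20c} declare intention to treat, which {20c} describes as "analysing all participants according to their original assignment, regardless of whether they completed the study". The sensitivity analyses in {20b} vary the missing-data assumption only. No between-arm model without the session covariate is stated.

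**The concern.** A covariate measured before randomisation can be adjusted for without changing what the arm coefficient means. One that arises afterwards, and that the assigned treatment can influence, cannot. If one type of coach secures more contacts, that is part of how well that type of coach works, and holding contacts fixed takes it out of the comparison.

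There is a second problem. Health and motivation plausibly drive both how many sessions a participant has and how the participant fares. The demographic covariates (age, sex, education, chronic diseases) capture these only in part. If coach type also affects session count, then among participants with equal counts the arms are no longer balanced on health and motivation, and randomisation no longer protects the comparison (collider bias).

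At stake is the meaning of every between-arm result. The trial wants to say whether lay coaching is as effective as professional coaching. As written, the model answers whether it would be as effective at the same number of sessions, and answers even that only if nothing unmeasured drives both sessions and outcome.

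**Working it through.** **The plan's own figures.** Sample size {14} gives f = 0.2, power 90%, alpha 0.05 and 30% dropout. For two equal groups d = 2f = 0.4. The F test has noncentrality f² × N; at N = 266 this is 0.04 × 266 = 10.64 and the power is 0.9015, so 266 reproduces. 266 / 0.70 = 380 also reproduces. Neither figure uses the session covariate.

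**Formula.** The document gives no session figures, so everything below is assumed. Work in SD units, lay minus professional:

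- a = arm difference in sessions
- b = effect of one SD of sessions on the outcome
- g, c = effects of an unmeasured factor (such as health or motivation) on sessions and on the outcome
- T = true total effect of assignment

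The unadjusted model estimates T. Adding sessions to a linear model gives

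adjusted = T − a × b − a × g × c = T − a × (b + g × c).

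The term a × b is the mediated part that is removed; a × g × c is the collider bias.

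**Results.** Each row was also simulated as a linear model with 380 participants and 1,500 runs. Rejection is of the hypothesis of no arm difference.

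| a | b | g × c | T | Formula | Simulated, adjusted | Rejection, unadjusted | Rejection, adjusted |
|---|---|---|---|---|---|---|---|
| 0 | 0.3 | 0 | −0.40 | −0.40 | −0.400 | 97.2% | 97.9% |
| −0.25 | 0.3 | 0 | −0.40 | −0.325 | −0.327 | 97.7% | 92.1% |
| −0.5 | 0.3 | 0 | −0.40 | −0.25 | −0.248 | 96.9% | 67.7% |
| −1.0 | 0.3 | 0 | −0.40 | −0.10 | −0.105 | 97.7% | 17.2% |
| −0.5 | 0.3 | 0.16 | −0.40 | −0.17 | −0.170 | 96.7% | 43.4% |
| −0.5 | 0.3 | 0 | 0 | +0.15 | +0.150 | 4.8% | 30.9% |
| −0.5 | 0.3 | 0.16 | 0 | +0.23 | +0.230 | 5.6% | 68.1% |
| −0.5 | 0 | 0.16 | 0 | +0.08 | +0.082 | 4.5% | 12.0% |

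Here g × c = 0.16 is 0.4 × 0.4. Row three in full: −0.40 − (−0.5 × 0.3) = −0.40 + 0.15 = −0.25.

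The last row is pure collider bias: sessions do nothing and there is no coach effect, yet the adjusted model shows a difference in favour of lay coaches. When a = 0 there is no shift.

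**Opposite direction.** By the same formula, if lay coaches achieve 0.5 SD more sessions and T = +0.40, the adjusted value is 0.40 − 0.5 × 0.3 = +0.25. Part of a lay advantage is then hidden.

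**The case against.** **Equal contact is a sensible question.** Section {11a} says procedure and format are the same in both arms and that only the coaches' clinical knowledge and experience differ. A comparison at equal contact would isolate that. This stands as a reason for a labelled secondary analysis. It does not support the covariate in the only between-arm model, because the stated objective is the effect of coach type and the equal-contact estimate stays open to confounding.

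Several stronger readings are tempting, but the document does not carry them:

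- *That the adjustment favours the hoped-for finding of no difference.* This needs lay coaches to deliver fewer sessions. The only statement on the matter, in {6a}, points to more engagement with lay coaches, in which case adjustment would work against them. The direction is unknown.
- *That the covariate contradicts the intention-to-treat statement.* Section {20c} speaks of analysing participants as assigned, and a covariate does not breach that. The departure is in the estimand, not in the analysis set.
- *That the retention section shows the number of sessions is negotiated.* In context, {18b} describes scheduling. That the number can vary follows from the floor in {11a} and the freedom to stop in {11b}.
- *That both models are wrong for the same reason.* Only the GEE is described as comparing arms. The argument reaches the ANCOVA only if one of its terms is used to compare arms.
- *That carrying baseline values forward makes matters clearly worse.* Participants with missing follow-up may have had few sessions, and their change is zero by construction. But the document does not say how many sessions they had, and the arm contrast is affected only if sessions differ by arm. This is secondary.

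**Conclusion.** The point holds for the between-arm GEE, across all primary and secondary outcomes. The choice of covariate is stated in the text, so it is not a detail left to an analysis plan, and none of the stated sensitivity analyses repairs it. The coefficient estimates coach type at equal contact, with possible collider bias, where the objective calls for the total effect of assignment.

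The size cannot be fixed from the document. Under the assumed moderate setting (sessions 0.5 SD lower with lay coaches, 0.3 SD of outcome per SD of sessions, no unmeasured common cause), a true −0.40 SD, the effect size used for planning, becomes −0.25 SD and rejection falls from 97% to 68%. With a true total effect of zero, the same setting rejects about 31% of the time. That is false rejection with respect to the total effect; the equal-contact effect in that setting really is +0.15 SD.

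The shift vanishes if coach type does not affect session count. It can hide a lay deficit if lay coaches achieve fewer contacts, and a lay advantage if they achieve more.

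**What to change.** In {20a}, remove session frequency from the main between-arm GEE, and from any repeated-measures ANCOVA term used to compare arms. Adjust only for baseline variables: the four stratification factors (age, sex, education, number of chronic diseases) and the baseline value of the outcome.

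Report session counts by arm as a process measure. The data already exist, because {11a} has every coach-participant interaction documented with date and time. Keep any session-adjusted model as a labelled exploratory analysis, with a statement that it assumes no unmeasured common cause of sessions and outcome.

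The cost is small but not nil. The trial is running under protocol version 1.0, so this is an amendment to be communicated as {25} describes, and it should be dated before the arms are compared. No new data are needed, and the sample sizes of 266 and 380 stand.
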